### Sample size calculation

Power analyses determined the sample size needed to compare the effect of IMARA-SA and control interventions on AGYW HIV/STI incidence and PrEP and HTC uptake. Because binary outcome variables pose the greatest challenge for power, we evaluated power for STI incidence (yes/no)—our primary outcome—across a range of prevalence estimates over 12-months. All calculations used a 2-sided test with alpha = .05. Based on data in the Plus Pills study, [103] using a Cox proportional hazards model with a range of incidence estimates, we will have ≥80% power to detect hazard ratios ≤0.5 for STI incidence ranging from 20 to 30%, even with 25% attrition. Effect sizes for binary outcomes is given in terms of the relative risk (RR), where RR = 1 indicates no treatment effect. A RR < 1 indicates a protective effect of the intervention. With 80% retention, we will have ≥80% power to detect RRs ≤ 0.38 when the proportion in the control group is 20%, and RRs ≤ 0.65 when the proportion in the control group is 50%. We also calculated the standard effect size (d) in standard deviations for group mean comparisons with 80% power for continuous outcomes, where d = 0 is defined as no treatment effect. We will be able to detect a small to medium effect size (d = 0.36) even with 75% retention. Low HIV incidence among AGYW (2.54%) per year will allow us to explore incidence, but we do not expect sufficient statistical power to test intervention effects on HIV incidence.

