South African FC may serve as a catalyst for AGYW change. Despite noting parents as the best source of information about sex and general receptivity to such discussions, only 20% of SA youth receive information about sex from their parents, and almost 50% of girls report that they could not openly discuss sexuality with their parents [44, 45]. Likewise, African mothers report needing and wanting accurate knowledge to discuss sex with their children [46]. Capitalizing on the FC-AGYW relationship, improving the quality of FC-AGYW conversations about sexual and reproductive health, teaching FC to use accurate information, and challenging cultural taboos that inhibit communication about sex [47] may alter the current HIV-trajectory for SA AGYW. Notably, AGYW may also be change agents for their FC who want to be positive role models for AGYW. In the process of promoting AGYW sexual and reproductive health, FC may change their own behavior (including HTC and PrEP uptake), thereby reducing their own risk for HIV.

IMARA is an evidence-supported mother-daughter (“mother” refers to any female caregiver) program based on the Social Personal framework [48] and derived from three established interventions: SISTA [49–53] and SiHLE [54] for African American women and girls respectively, and Project STYLE for teens and families in mental health care [55]. SISTA and SiHLE address the importance of relationship power and gender dynamics as drivers of HIV risk behavior. This is critical for the South African context where AGYW’s first and ongoing sexual partner is typically an older male, [56] and AGYW with older partners are four times more likely to test positive for a sexually-transmitted infection (STI), [57] report transactional sex, [57] and have high HIV infection rates [58]. In addition, gender-based violence (GBV) among SA AGYW is higher than in every other region in sub-Saharan Africa, [44, 59, 60] and is related to high rates of STI [61] and HIV-risk, [62–64] and impedes women’s ability to receive HTC, link to treatment, and adhere to PrEP [65–67]. Project STYLE emphasizes parent-teen relationships and communication as protective against HIV and STI risk. A recent efficacy study of IMARA in the US [68] revealed a 43% reduction in incident STI infections at 1-year follow-up among 14–18 year-old African American girls who received IMARA compared to a time-matched health promotion program (*p* = .011).

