### Study objectives

The purpose of this study is to test the effectiveness and cost-effectiveness of a culturally-tailored, evidence-based, HIV/STI prevention program for SA AGYW and FC. We will randomly assign 525 AGYW-FC dyads to IMARA-SA (*n* = 263) or a family-based health promotion (HP) program (*n* = 262) matched in time and intensity and compare participants on incident STI, and HTC and PrEP uptake at 6 months. Secondary objectives are to assess intervention effects on the primary outcomes at 12 months, reported non-condom use, number of partners, HIV incidence, and adherence to ART/PrEP. We will also evaluate the costs and CE of IMARA with respect to the acquisition of STI and HIV where possible, considering power limitations.

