### Randomization

We will use a 1:1 randomization allocation to assign FC-AGYW dyads to treatment arm (IMARA-SA *n* = 263 or HP *n* = 262) following the baseline assessment. The AGYW will select a colored paper from a hat that determines the family’s group assignment. Assessors but not intervention staff will be blinded to treatment arm at 6- and 12-month follow-up.

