#### Primary outcomes

At 6-month follow-up, we will examine AGYW STI incidence (gonorrhea, chlamydia, and trichomoniasis), PrEP uptake and 1-month supply of medication, and HTC uptake.

Secondary Outcomes: At 12-month follow-up, we will examine AGYW STI incidence (gonorrhea, chlamydia, and trichomoniasis), PrEP prescription and 1-month supply of medication, and HTC uptake. At 6- and 12-month follow-up, we will assess AGYW sexual behavior (e.g., condom use, substance use during sex, number of partners, concurrent partners), using the AIDS Risk Behavior Assessment, [82] HIV incidence via HTC, and self-reported adherence to ART and PrEP (where appropriate) using Wilson’s 3-item scale [83]. We will use standard cost evaluation methods [84, 85] to assess IMARA-SA’s costs, including personnel time and non-personnel resources (e.g., travel expenses, snacks, incentives, curricular materials).

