We believe the study design has several strengths. We will leverage FC and the FC-AGYW relationship to support HTC and PrEP uptake and linkage to care (where appropriate). Although AGYW are the primary focus of the program, IMARA-SA targets both FC and AGYW to support one another in prevention efforts. The design offers a combination package that includes behavioral and biomedical intervention strategies and provides on-site access to HTC, PrEP, and STI treatment, eliminating typical barriers to service. Furthermore, we believe that IMARA-SA is responsive to the age, gender, and cultural needs of the population. Although originally designed and tested with African American 14–18-year-old girls in the US, our systematic approach to adaptation for the South African local context increases confidence in its local relevance. This study is among the first to evaluate the impact of a FC-AGYW intervention on HTC and PrEP uptake using a rigorous and culturally adapted trial of sufficient size to detect effects on AGYW STI incidence and explore HIV incidence. We consider it a potential innovation in the HTC and PrEP uptake environment, which given the smooth access to services, close collaboration with clinic partners, and brief intervention format (approximately 10 h), is well positioned for scale. IMARA-SA was designed to meet the standard for evidence-based interventions, advance intervention science with SA AGYW, and prepare for sustainability by engaging key stakeholders at the start and documenting the costs.

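### The stated power of at least 80% for STI incidence is worked out over 12 months, but the primary STI outcome is at 6 months, where power for a hazard ratio of 0.5 is about 49-80%

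*Protocol article*

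**What the plan says.** The Sample size calculation section names STI incidence as the primary outcome and says its power was evaluated "across a range of prevalence estimates over 12-months". It then cites an earlier study and a Cox model and concludes: "we will have ≥80% power to detect hazard ratios ≤0.5 for STI incidence ranging from 20 to 30%, even with 25% attrition". On the error rate it says "All calculations used a 2-sided test with alpha = .05". The Cox sentence does not say whether 20-30% is the control-arm risk or the risk pooled over arms. It also does not repeat the period; 12 months comes from the sentence on the yes/no outcome shortly before it.

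The Primary outcomes section sets a different time point: "At 6-month follow-up, we will examine AGYW STI incidence (gonorrhea, chlamydia, and trichomoniasis". The Methods part of the Abstract and the Study objectives agree that the primary comparison is at 6 months, and all three places list the 12-month STI result as secondary. The article gives neither a 6-month incidence nor a 6-month power. The Discussion describes a "trial of sufficient size to detect effects on AGYW STI incidence" without naming a time point.

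**The concern.** The power labelled as that of the primary outcome is computed on the horizon of a secondary outcome. Fewer infections will have occurred by 6 months than by 12, and power in a time-to-event comparison depends on the number of events. The primary comparison could therefore have clearly less than the advertised power.

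A reader who takes the 80% at face value would give a non-significant 6-month result more weight as evidence against an effect than the design supports. Because the article makes a definite power claim and attaches it to the primary outcome, this is more than a detail left to the analysis plan.

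**Working it through.** **Inputs from the protocol article**
- Sample: "We will randomly assign 525 AGYW-FC dyads to IMARA-SA" or control (Study objectives); "We will use a 1:1 randomization allocation" (Randomization).
- Two-sided alpha 0.05, hazard ratio (HR) 0.5, incidence 20-30%, attrition 25% (Sample size calculation).
- Retained: 525 × 0.75 = 393.75, or about 197 per arm.

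**Assumptions the article does not give**
- Arm for the 20-30%: both readings are shown.
- Constant hazard over the 12 months.
- Attrition already reached by 6 months: 25% in the main case, none as the opposite extreme.

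**Formulas**
- Treated risk = 1 − (1 − control risk)^0.5.
- 6-month risk = 1 − (1 − 12-month risk)^0.5.
- Events E = retained number × mean of the two arm risks.
- Power (Schoenfeld) = Φ(√E/2 × |ln HR| − 1.96).
- Events needed for 80% power at HR 0.5: 4 × (1.96 + 0.842)² / (ln 0.5)² = 65.3, so 66.

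**Step 1: the plan's own figure, at 12 months**
- Pooled reading: E = 393.75 × 0.20 = 78.8 and 393.75 × 0.30 = 118.1. Power is 86.8% and 96.5%. The stated 80% or more reproduces.
- Control-arm reading: treated risks are 10.6% and 16.3%. E = 393.75 × (0.200 + 0.106)/2 = 60.2 and 393.75 × (0.300 + 0.163)/2 = 91.2. Power is 76.7% and 91.2%. The claim fails by about 3 points at 20% and holds only from about 22%.

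**Step 2: the same calculation at 6 months, 25% attrition**
- Control-arm reading: control risk 10.6% and 16.3%, treated risk 5.4% and 8.5%. E = 31.5 and 49.0. Power is Φ(−0.016) = 49.4% and Φ(0.465) = 67.9%.
- Pooled reading: pooled 20% and 30% at 12 months with HR 0.5 imply 12-month control risks of 26.0% and 38.5%. At 6 months these become control 14.0% and 21.6%, treated 7.3% and 11.4%. E = 41.8 and 64.9. Power is Φ(0.281) = 61.1% and Φ(0.832) = 79.7%.
- Events relative to 12 months: 31.5/60.2 = 52%, 49.0/91.2 = 54%, 41.8/78.8 = 53%, 64.9/118.1 = 55%.

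**Step 3: no loss at all by 6 months (525 evaluable)**
- Control-arm reading: E = 42.0 and 65.3; power 61.2% and 80.0%.
- Pooled reading: E = 55.8 and 86.6; power 73.5% and 89.7%.

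| Power for HR 0.5, at 20% to 30% incidence | Control-arm reading | Pooled reading |
|---|---|---|
| 12 months, 25% attrition | 77-91% | 87-97% |
| 6 months, 25% attrition | 49-68% | 61-80% |
| 6 months, no loss | 61-80% | 74-90% |

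**Step 4: effect detectable with 80% power at 6 months, 25% attrition**
- Solve √E(h)/2 × |ln h| = 1.96 + 0.842, where E(h) = 393.75 × [c + 1 − (1 − c)^h]/2 and c is the 6-month control risk from step 2.
- Control-arm reading: HR about 0.35 (20%) to 0.44 (30%).
- Pooled reading, with its control risks held: HR about 0.41 to 0.50.

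**The case against.** Four arguments stand against the point or its size.

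- **The low range is only one reading.** A reader might infer that 6-month power is simply 49-68%. The documents do not support this as the single answer. It requires 20-30% to be the control-arm risk, and on that reading the article's own 12-month claim fails at 20%. The pooled reading, on which the claim reproduces, gives 61-80% and misses 80% at its upper end by only 0.3 points. Full attrition at the first follow-up is also pessimistic: at 80% retention, the other figure the section uses, the pooled upper end is 69.2 events and about 82% power. This stands, and the range has to be given with its assumptions.
- **The period of the 20-30% is inferred.** If it were a 6-month incidence, the gap would close. But the only period the section gives for the STI power evaluation is 12 months, so the text as written supports the mismatch.
- **The section also gives a detectable relative risk of 0.38 at a 20% control proportion with 80% retention.** That statement has no time point and rests on a control proportion above the 10.6-16.3% implied at 6 months on the control-arm reading. It does not supply the missing 6-month power.
- **The 12-month outcome, Cox models and analyses combining time points are already planned.** A null 6-month result would therefore not stand alone, and calling it uninformative would go too far.

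A reader might also argue that power is lower still because the earlier US study "revealed a 43% reduction in incident STI infections at 1-year follow-up", an effect weaker than an HR of 0.5. The Background does not give that reduction as a hazard ratio, and the program has since been adapted to another setting. No power figure is drawn from it here.

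**Conclusion.** The mismatch is wrong as written: the at-least-80% claim is labelled as power for the primary outcome but belongs to the 12-month secondary horizon. At the article's own 25% attrition, and with a constant hazard, power for an HR of 0.5 at 6 months lies between about 49% and 80%, depending on whether 20-30% is a control-arm or pooled risk. Neither reading reaches 80%.

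If nobody were lost by 6 months, the favourable end would reach or pass 80%. At 20% incidence, power would still be 61% or 74%, so it stays below 80% on every reading of the 12-month figure.

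The multiplication in the plan is not itself at fault, since the stated figure reproduces at 12 months on the pooled reading. Nor does it follow that the primary endpoint must change. What is established is that the stated power does not describe the stated primary outcome.

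**What to change.** Keep the 6-month primary STI outcome and revise the Sample size calculation section:

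1. State the assumed 6-month STI incidence, and whether it is the control-arm risk or pooled over arms.
2. Restate the power for an HR of 0.5 at 6 months (about 49-80% at 25% attrition on the assumptions above), or give the effect detectable with 80% power at 6 months.
3. Label the existing figure of at least 80% as applying to the 12-month secondary outcome.
4. Qualify the sentence in the Discussion on sufficient size so that it names the time point and the effect it refers to.

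The sponsor could instead make cumulative STI incidence through 12 months the primary outcome, decided before outcome data are seen. Urine testing at both visits is already planned. That is a design choice with its own costs (a primary readout six months later, and dilution of any effect confined to the early months) and is not needed to cure the mismatch.

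The recommended change is to wording only. Its cost is a less favourable stated power.

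### The power figures in the sample size paragraph do not share one basis: the RR and d values imply about 120 effective participants per arm, while the hazard ratio line does not use that size

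*Protocol article*

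**What the plan says.** Study objectives: "We will randomly assign 525 AGYW-FC dyads to IMARA-SA" (263) or health promotion (262). Randomization: "We will use a 1:1 randomization allocation to assign FC-AGYW dyads to treatment arm".

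Sample size calculation makes these statements in one paragraph:

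- Common basis: "All calculations used a 2-sided test with alpha = .05".
- Cox model: at least 80% power for hazard ratios of 0.5 or lower, for STI incidence of 20 to 30%, with 25% attrition.
- Binary outcomes: "With 80% retention, we will have ≥80% power to detect RRs" at two control proportions, namely "RRs ≤ 0.38 when the proportion in the control group is 20" per cent, and "RRs ≤ 0.65 when the proportion in the control group is 50" per cent.
- Continuous outcomes: "We will be able to detect a small to medium effect size", namely d = 0.36, at 80% power and 75% retention.
- Direction: "A RR < 1 indicates a protective effect of the intervention". No RR above 1 is given, although the paragraph opens by saying that the calculations also cover PrEP and HTC uptake.

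The paragraph states no ICC or design effect. Under Intervention delivery, cohorts are about 16 dyads. Under Statistical analysis, random intercepts for clustering are to be used if needed.

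**The concern.** Read together, the lines pull apart. At a 20% control risk, a hazard ratio of 0.5 is a risk ratio of about 0.53. The Cox line thus offers at least 80% power at RR 0.53 with 75% retained, while the next lines give 0.38 as the value reached with 80% retained. A better-retained sample should not need a much larger effect, so the two lines appear to rest on different effective sample sizes.

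What is at stake is how the result will be read. If the RR and d lines carry a clustering allowance that the Cox line lacks, the power claim for STI incidence is too high. If there is no such allowance, the RR and d lines undersell the trial. These readings bear differently on a null STI result. Separately, benefit on two of the three primary outcomes, HTC and PrEP uptake, is an RR above 1, and no detectable value is printed in that direction.

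**Working it through.** **Inputs from the protocol article.** N = 525, 1:1; two-sided alpha 0.05 (z = 1.960); 80% power (z = 0.842). Analysed per arm: 525 × 0.80 / 2 = 210 for the RRs; 525 × 0.75 / 2 = 196.9 for d and HR.

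**1. Can the printed RRs be reproduced?** Pooled two-proportion formula, with p̄ the mean of p1 and p2:

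n per arm = [1.960·√(2p̄(1−p̄)) + 0.842·√(p1(1−p1) + p2(1−p2))]² / (p1−p2)²

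- RR 0.38: 20% v 7.6%, p̄ = 0.138. n = (1.960×0.4878 + 0.842×0.4798)² / 0.124² = 120.3. Enrolled at 80% retention: 2 × 120.3 / 0.80 = 301.
- RR 0.65: 50% v 32.5%, p̄ = 0.4125. n = (1.960×0.6962 + 0.842×0.6851)² / 0.175² = 123.0. Enrolled: 308.

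Rounding n up to whole participants gives 303 and 310. A continuity correction gives 136 and 135 per arm, or 340 and 338 enrolled.

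**2. Can the printed d be reproduced?** n per arm = 2(2.802/0.36)² = 121.1. Enrolled at 75% retention: 323 (325 after rounding up).

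So none of the three is the 80%-power value for 525 dyads, yet all three point to 120–123 effective participants per arm. The implied design effects are 210/120.3 = 1.75, 210/123.0 = 1.71 and 196.9/121.1 = 1.63.

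**3. What 525 dyads give without clustering**

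| Effect | Printed | Power at printed value | 80%-power value |
|---|---|---|---|
| RR, control 20%, 210 per arm | 0.38 | 96.0% | 0.51 |
| RR, control 50%, 210 per arm | 0.65 | 95.6% | 0.73 |
| d, 197 per arm | 0.36 | 94.7% | 0.28 |

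In the uptake direction, at 210 per arm, the 80%-power values are RR 1.60 (20% v 32%) and RR 1.27 (50% v 63.5%).

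Other settings do not recover the printed set. Alpha 0.025 gives 0.47, 0.70 and 0.31. Alpha 0.0167 gives 0.45, 0.69 and 0.33, and so does 90% power. Power of 95% comes close (0.39, 0.66, 0.36), but the text says 80%.

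**4. The hazard ratio line.** Schoenfeld: power = Φ(|ln 0.5|·√(events/4) − 1.960); 80% power needs 66 events. Analysed: 525 × 0.75 = 393.75. The text does not say whether 20–30% is control-arm or overall incidence, so both are shown.

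- Control-arm 20%: the intervention arm has 1 − 0.8^0.5 = 10.56%, RR 0.53. Events = 196.9 × (0.20 + 0.1056) = 60.2.
- Overall 20%: events = 393.75 × 0.20 = 78.75.
- Control-arm 30%: the intervention arm has 1 − 0.7^0.5 = 16.33%. Events = 91.2.
- Overall 30%: events = 118.1.

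| Incidence | Meaning | Power, no clustering | Power, design effect 1.75 |
|---|---|---|---|
| 20% | control arm | 76.7% | 52.9% |
| 20% | overall | 86.8% | 64.2% |
| 30% | control arm | 91.2% | 70.6% |
| 30% | overall | 96.5% | 81.3% |

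The design effect is applied by dividing the events by 1.75, for example 60.2 / 1.75 = 34.4.

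**The case against.** **The sentences are literally true.** A claim of at least 80% power is met by 96%, and power at RR 0.38 does not exclude power at RR 0.53. This stands. A reader might infer that the RR and d lines claim power the trial lacks, or that they flatly contradict the hazard ratio line. They do neither. They are conservative bounds, given in a form usually taken as the smallest detectable effect.

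**A clustering allowance may have been built in.** A reader might infer that the figures were left over from a design of about 300 dyads. The documents do not support choosing that explanation. At 300 dyads and 75% retention, d would be 0.37, not 0.36. An assumed ICC of 0.05 (not in the documents) with 16 dyads per group gives a design effect of 1 + 15 × 0.05 = 1.75, which reproduces both RRs (0.379 and 0.646). It gives d = 0.36 at 80% retention, though 0.37 at the stated 75%. An article may also leave an ICC to the full protocol, so its absence alone is no fault. What remains is that the hazard ratio claim fails at the low end of its range once the same allowance is applied, on either meaning of incidence.

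**RR below 1 is natural for STI incidence**, which this section calls its primary outcome. That is fair, and it makes the direction point secondary. The paragraph does, however, name PrEP and HTC uptake among the outcomes powered.

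**Conclusion.** The point holds as an inconsistency of basis. No single effective sample size produces the RR and d values as 80%-power limits and also supports the hazard ratio claim over its whole range. Without clustering, 525 dyads detect RR 0.51, RR 0.73 and d = 0.28 at 80% power, and the printed values are overly cautious. With a design effect near 1.75 the RRs are right, but power for HR 0.5 is 53–71% (control-arm incidence) or 64–81% (overall incidence). Dropping clustering does not fully rescue the Cox line: at 20% it has about 77% power if that is control-arm incidence, and 87% if overall.

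A reader might go further and infer that the detectable effect is unknowable or that the trial is the wrong size. Neither follows, because the effects can be computed under each stated assumption and no change to 525 is implied. The results rest on the pooled normal approximation, Schoenfeld's formula and, for the clustered variant, an assumed design effect. This should be fixed, but it alters no estimand, analysis or conduct.

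**What to change.** Recompute the whole paragraph from N = 525, with the retention stated for each figure and one explicit clustering assumption.

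- **If no clustering was assumed:** print RR 0.51 (control 20%) and RR 0.73 (control 50%) at 80% retention, and d = 0.28 at 75% retention. Either say that 20–30% is overall incidence or restate the HR 0.5 claim at the 20% end.
- **If clustering was assumed:** state the ICC, group size and design effect, apply the same factor to the hazard ratio line, and restate its power.
- **In either case:** give detectable effects for HTC and PrEP uptake above 1. Without clustering these are RR 1.60 at a 20% control proportion and RR 1.27 at 50%.

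The cost is about an hour of recalculation and one corrected paragraph, with no change in sample size.
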